### Overall design

We propose a cluster-randomised trial with hybrid type III design, incorporating a twofold emphasis on the effectiveness of the implementation strategy (WP3 and WP4) and the outcome of the clinical intervention (WP4 and WP5) [30]; the scheme for crucial events is as in Fig. 2.

**Fig. 2 Fig2:**
[figure not shown]
The overall points of time for inclusion, randomisation and data collections across OPTION

### Setting and inclusion criteria

The research team called upon orthopaedic units in university, regional, and local hospitals across Sweden. To avoid excess travel during data collections and enable participation in the intervention, the hospitals furthest north and south were contacted last. All 55 potential sites are equivalent in funding, either run by the public sector or company-driven hospitals with regional procurements. Further, they were considered equal, regardless of providing hip fracture surgery and elective hip replacements or elective hip replacement surgery only. A sample of 20 orthopaedic units was deemed necessary to provide sufficient statistical strength to detect an impending increase in adherence to the guidelines in the intervention group.

The sites were contacted by the research team with information and were engaged as a result of each head of department consenting to the OPTION study. Reasons for declining to participate concerned primarily staffing issues or heavy workload due to the pandemic (in some cases requiring orthopaedic units to transform into COVID-19 units).

### Power and sample

The study power calculation is based on opportunities to detect an impending increase in adherence to national bladder monitoring guidelines: assuming an absolute increased adherence to the guidelines of 15% (50% in the control group and 65% in the intervention), the required sample size is 227 patients in each arm, with 90% power and two-sided significance level of 0.05 (based on an intracluster correlation coefficient of 0.03). With 10 clusters in each arm and an average cluster size of 70 patients, a total of 1380 patients are needed. Considering a dropout rate of 10%, a total sample size of 1500 is required, providing an average cluster size of 75 patients. With a variance between around 5% and 80% incidence of urinary retention among hip surgery patients, it is difficult to calculate power based on this factor. Yet, considering that it may be 35–40%, the cluster size suggested above will also allow detecting a 15% absolute difference in incidence of urinary retention between the intervention group and the control group post intervention.

Once the units had agreed and the ethics board had approved the trial, the randomisation was performed. To prevent bias in terms of complexity of the patients’ medical status, and influence of clinical training programmes for students in nursing science and physio- and occupational therapy, university hospitals were equally distributed as intervention and control units. Further, two units located in Stockholm, the capital of Sweden, were randomised to either intervention or control. Thus, the randomisation was completed in four steps: university units, units in the Stockholm catchment area, and regional orthopaedic and local orthopaedic units, respectively, drawn from sealed envelopes by an impartial researcher engaged for this procedure whilst monitored over video link by the research team.

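### The sample-size chain is mis-stated: 227 per arm contains no clustering, 1380 is not 20 sites of 70, 1500 does not cover 10% loss, and the 90% power rests on a normal approximation for 20 sites

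*Protocol article*

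**What the plan says.** All the figures stand in the Power and sample section of the protocol article.

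- The target is guideline adherence of "50% in the control group and 65% in the intervention".
- For this, "the required sample size is 227 patients in each arm, with 90% power and two-sided significance level of 0.05", and the same sentence says in brackets that the figure is "based on an intracluster correlation coefficient of 0.03".
- The next sentence gives the clustered total: "With 10 clusters in each arm and an average cluster size of 70 patients, a total of 1380 patients are needed".
- Then comes the allowance for loss: "Considering a dropout rate of 10%, a total sample size of 1500 is required, providing an average cluster size of 75 patients".

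The section states no small-sample allowance for the number of sites and no figure for how much site sizes vary.

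**The concern.** Consecutive sentences do not agree with one another. The first credits 227 per arm with an allowance for clustering, although 227 is what a textbook two-proportion formula gives without one. The second gives a total that is not the product of its own number of sites and site size. The third allows for 10% loss, yet the number left falls below the number said to be needed.

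There is also the question of what the 90% means. The randomised unit is the site and there are 20 of them. An analysis that respects this estimates the between-site variation from 20 sites, and a normal approximation does not charge for that.

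This is the sample-size justification for the primary outcome. A reader who takes the first sentence at face value would put the per-arm requirement at about a third of what it is. The stated power is also what later readers will use to judge the precision of the result.

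**Working it through.** **Inputs (all from Power and sample).** Control 0.50, intervention 0.65, difference 0.15; power 90%; two-sided 0.05; ICC 0.03; 10 sites per arm; site size 70; clustered total 1380; loss 10%; final total 1500, or 75 per site.

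**1. Reproduce 227.** Two-proportion formula with pooled variance under the null, mean proportion 0.575:

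n = [1.960·√(2 × 0.575 × 0.425) + 1.282·√(0.50 × 0.50 + 0.65 × 0.35)]² / 0.15² = 226.2, rounded up to 227 per arm.

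No ICC is involved. The arcsine version also gives 227, the unpooled version 223, and a continuity correction 240.

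**2. What 227 per arm would deliver in 10 sites.** Site size is 22.7, so the design effect is 1 + 21.7 × 0.03 = 1.651 and the effective size is 227/1.651 = 137.5 per arm. Power is about 72% by the normal approximation and about 67% with t on 18 df.

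**3. Reproduce 1380.** Design effect = 1 + (m − 1) × 0.03.

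| Site size m | Design effect | 227 × design effect, per arm | Two arms | 20 × m |
|---|---|---|---|---|
| 69 | 3.04 | 690 | 1380 | 1380 |
| 70 | 3.07 | 697 | 1394 | 1400 |

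So 1380 belongs to 69 per site. The ICC is used here, one step later than the text says.

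**4. Loss.** 1500 × 0.90 = 1350, which is 30 short of 1380. To keep 1380 after 10% loss takes 1380/0.90 = 1533.3, so 1534. The loss that 1500 can absorb is 1 − 1380/1500 = 8%.

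**5. Power, equal sites, ICC 0.03.** Effective size per arm is 10m divided by the design effect. The normal result uses the critical value 1.960. The t result uses a non-central t with 20 − 2 = 18 df, critical value 2.101. Ranges run over pooled and unpooled variance.

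| Analysed | m | Design effect | Effective n per arm | Normal | t, 18 df |
|---|---|---|---|---|---|
| 1350 | 67.5 | 2.995 | 225.4 | 89.6% to 90.3% | 86.1% to 86.9% |
| 1380 | 69 | 3.04 | 227.0 | 89.8% to 90.5% | 86.3% to 87.1% |
| 1500 | 75 | 3.22 | 232.9 | 90.6% to 91.2% | 87.2% to 87.9% |

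The plan's 90% therefore reproduces under the normal approximation, even at 1350. The slips in steps 3 and 4 cost almost no power. The roughly three-point gap comes from the reference distribution.

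**6. Sensitivity to site size (assumed values).** With design effect 1 + [(1 + CV²)m − 1] × 0.03, 1350 analysed and 18 df, power is about 83% for a coefficient of variation (CV) of 0.4 and about 79% for 0.6. The document gives no figure for this variation, so these show direction only.

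**The case against.** The strongest reply is that the calculation did allow for clustering. The sentence after 227 applies the design effect, 2 × 227 × 3.04 = 1380, and the usual design-effect method then returns 90%. On this view the bracket about the ICC is attached to the wrong number, the other slips are 1% to 2%, and the working target of 1500 is unaffected. That stands. It rules out the stronger reading, which a reader might infer, that the ICC was left out of the design.

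A second reply is that the 87% rests on a t reference with 18 df, which the document does not name, and that the design-effect formula with a normal approximation is a standard planning method. This also stands in part: 87% is the power of an unadjusted analysis that estimates between-site variation from 20 sites, not a figure the plan contradicts. But the sites are what was randomised and there are only 20, so the allowance is a fair one to ask for.

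A third reply is that baseline adherence is collected at every site (Data collection), and adjusting for it could recover the loss. The document gives no correlation. As an illustration, suppose that baseline site adherence explained 20% of the between-site variance. With 1350 analysed, equal sites and 17 df, power would be about 91%; at 30% it would be about 93%. So a reader might infer that 87% is a ceiling, and the documents do not support that. Even without adjustment, 1500 analysed gives up to 88%.

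The lower figures of 83% and 79% rest on assumed site-size variation. An average cluster size by itself does not show that sites differ materially, so those figures cannot be presented as the power of this trial.

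None of these replies rescues the sentence that ties 227 to the ICC, the mismatch of 1380 with 20 × 70, or the loss step.

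**Conclusion.** The chain is wrong as written in three places: 227 per arm is the size before clustering; 1380 corresponds to 69 per site and not 70; and 1500 less 10% is 1350, so 1500 covers about 8% loss to 1380. The first is a serious mislabelling if read literally (about 67% to 72% power), but the next step corrects it in substance. The other two are small.

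The 90% holds under the normal approximation with equal sites. Allowing for only 20 randomised sites, with t on 18 df, equal sites, ICC 0.03 and no baseline adjustment, it is about 86% to 87% at 1350 analysed and 87% to 88% at 1500. It would be lower with unequal sites, by an amount the document does not let anyone compute, and could be higher with baseline adjustment. The document does not support a claim that the trial is badly underpowered. The figures should be restated, since they justify the size of the trial for its primary outcome.

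**What to change.** In Power and sample:

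1. Label 227 per arm as the size before clustering.
2. Move the ICC of 0.03 to the clustered total and show the design effect: either 69 per site, design effect 3.04, about 690 per arm and 1380 in total; or 70 per site, design effect 3.07, about 697 per arm and 1394 in total (1400 with 20 full sites).
3. State that 1500 recruited leaves 1350 after 10% loss, or that 1500 allows about 8% loss to 1380.
4. State power as about 87% for an unadjusted analysis of 20 sites of equal size, and say that unequal sites lower it. If a baseline-adjusted analysis is used, quote its power instead, with the assumed share of between-site variance that baseline explains.

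This needs no extra patients. A cap on patients per site is not needed and could lose patients, because with a cap of 75 the total of 1500 is reached only if all 20 sites fill it. The only cost is a slightly less favourable stated power.

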### Data analysis

Data from patients’ records, the Alberta Context Tool questionnaire, the patient survey on voiding difficulties, and patient participation will be analysed with statistical analyses [46]. Between-group differences will be analysed using Student’s independent-sample t test for continuous variables, the Mann–Whitney U test for non-normally distributed continuous variables, and a χ2 test for nominal variables.

Qualitative content analysis will be applied for all interviews [47, 48], subsequently transcribed verbatim to text files by a professional service.

All data will be considered in the final mixed methods [49], embedding the process evaluation [50].

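### Sites were randomised in four strata, but the named between-group tests carry no stratum term; once clustering is handled, leaving the strata out forgoes precision

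*Protocol article*

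**What the plan says.** Under Power and sample, the protocol article describes the allocation of the 20 sites: "Thus, the randomisation was completed in four steps: university units, units in the Stockholm catchment area, and regional orthopaedic and local orthopaedic units". For one stratum it also gives a reason and a result. To guard against imbalance in case mix and in student teaching, "university hospitals were equally distributed as intervention and control units". Two Stockholm units formed a stratum of their own. No reason, size or split is given for the regional and local strata.

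The Data analysis section opens its statement of tests with "Between-group differences will be analysed using". It lists the independent-sample t test, the Mann–Whitney U test for non-normal continuous variables and the χ2 test for nominal variables. It mentions no stratum, site effect or adjustment.

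The sample size assumes adherence of "50% in the control group and 65% in the intervention", "with 90% power and two-sided significance level of 0.05", and it is "based on an intracluster correlation coefficient of 0.03". It takes no credit for stratification.

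**The concern.** When sites are allocated in balance within strata, differences between strata largely drop out of the comparison between arms. An analysis without the strata leaves those differences in its error term. Its standard error is then too large, the test rejects less often than its nominal level, and power is lost. With 10 sites per arm, site-level precision is the scarce resource.

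This mechanism operates in an analysis that treats the site as the unit of variation. It does not describe the net behaviour of a patient-level χ2 or t test, where ignored clustering dominates and errs in the other direction. The point therefore concerns what the between-arm analysis should contain once clustering is dealt with.

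**Working it through.** **The plan's own figures.** The inputs are all in Power and sample: 50% v 65%, two-sided 5%, 90% power, ICC 0.03, 10 sites per arm.

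- Pooled-variance formula: n = [1.96·√(2·0.575·0.425) + 1.2816·√(0.25 + 0.2275)]² / 0.15² = 226.2, rounded up to 227. This agrees with "the required sample size is 227 patients in each arm".
- Design effect 1 + (m − 1)·0.03: m = 69 gives 3.04, and 2·227·3.04 = 1380. With m = 70 it is 3.07 and the total is 1394. The plan says "With 10 clusters in each arm and an average cluster size of 70 patients, a total of 1380 patients are needed", so its figure reproduces closely, and no stratum term is needed to reach it.

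**The stated χ2 test run on patients.** With a design effect of 3.07, its actual type I error is 2·[1 − Φ(1.96/√3.07)] = 26.3%. In simulation (20 sites of 70, ICC 0.03, assumed stratum sizes 6/2/6/6) it was about 26%, 22%, 17% and 11% when strata explained 0%, 25%, 50% and 75% of between-site variance. It is anti-conservative throughout.

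**A site-level test, with and without strata.** Assumptions:

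- 67.5 analysed patients per site (75 less the planned 10% dropout)
- ICC 0.03
- equal splits within strata
- a share f of between-site variance explained by strata; f is not in the document

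Steps:

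1. The variance of a site mean is proportional to 0.03 + 0.97/67.5 = 0.0444. The design effect is 1 + 66.5·0.03 = 2.995. The standard error of the difference including stratum variation is √(0.4775·2.995/675) = 0.0460.
2. The fraction of variance left after removing strata is r = 1 − f·0.03/0.0444, which is 0.865, 0.730 and 0.594 for f = 0.2, 0.4 and 0.6. The true standard error is 0.0460·√r = 0.0428, 0.0393 and 0.0355.
3. Unadjusted test, 18 df, critical value 2.101: actual type I error ≈ 2·P(t18 > 2.101/√r).
4. Unadjusted power ≈ P(T > 2.101/√r), where T is non-central t on 18 df with non-centrality 0.15/(0.0460·√r). The smaller true standard error enters here too, so this power rises with f.
5. Adjusted power: non-central t on 20 − 4 − 1 = 15 df, critical value 2.131, same non-centrality.

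| Assumed f | Type I error, no strata | Power, no strata | Power, with strata |
|---|---|---|---|
| 0 | 5.0% | 86.9% | 86.1% |
| 0.2 | 3.7% | about 88% | about 90% |
| 0.4 | 2.4% | about 90% | about 94% |
| 0.6 | 1.4% | about 92% | about 98% |

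From the unrounded values, the gains are about 2, 4–5 and 6 points. At f = 0 there is a loss of about 1 point.

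**Cross-check.** The same simulation, at f = 0, 0.25, 0.5 and 0.75, gave type I error of 4.9%, 3.3%, 1.7% and 0.5% without strata and 5.0%, 5.0%, 5.1% and 5.4% with them. Power was 85%, 87%, 90% and 92% without strata and 84%, 90%, 96% and 99% with them. Stratum sizes of 4/2/6/8 gave similar results.

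**The case against.** The case against has five parts.

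- **The harm is not in the tests as written.** A reader might infer that the stated χ2 or t test is conservative because strata are missing. That is not supported. Run on patients, these tests overstate precision, and omitting strata only partly offsets the inflation. The loss appears once clustering is handled. This stands, and it limits the point to the corrected analysis.
- **The size is assumed.** No figure in the document says how much between-site variance the strata explain, and the primary outcome is guideline adherence, not a clinical measure. The effect could be nil, in which case adjustment costs about 1 power point. This also stands.
- **The stated rationale is narrow.** One might infer that all four strata were chosen as prognostic and split evenly. The document gives a prognostic reason and an equal split for university hospitals only. The calculation therefore assumes balance in the other strata.
- **The trial is not short of patients on this account.** The 227, 1380 and 1500 figures use the ICC without any credit for strata. Reading the omission as underpowering against the plan, or as a source of false positives, would be wrong.
- **The analysis plan may already cover it.** A short article need not spell out the model, and the full plan is not shown. But the Data analysis section does not merely stay silent: it names two-group tests without strata. If a fuller plan includes the strata, the two texts need to be reconciled.

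**Conclusion.** The point holds in a limited form. Allocation was restricted by four strata, and the named tests do not reflect this. In an analysis that respects clustering, omitting the strata would make a nominal 5% test run at about 3.7%, 2.4% or 1.4% and forgo about 2, 4–5 or 6 points of power, if strata explain 20%, 40% or 60% of between-site variance. These figures rest on the planned ICC of 0.03, 67.5 analysed patients per site and equal splits within strata. The variance shares are assumptions. The direction is sound whenever strata explain a material share; the size is unknown.

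This is secondary to the clustering fault. Correcting clustering alone, say with an 18-df site-level test, would leave it in place.

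**What to change.** In the between-arm analysis that accounts for clustering (a site-level analysis, or a mixed model with small-sample degrees of freedom), include the randomisation stratum (university, Stockholm, regional, local) as a fixed effect. Apply this to the primary outcome and to the additional quantitative between-arm comparisons. State 15 residual degrees of freedom at site level, before any other site-level covariates. If an analysis plan already says this, amend the Data analysis wording to agree with it.

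The cost is one sentence and 3 degrees of freedom (18 to 15), worth about 1 power point if the strata explain nothing. It needs no new data and no change to the design, because stratum membership was fixed at randomisation.

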### Participants

#### Patients

Patients undergoing hip surgery in any of the orthopaedic units (whether control or intervention groups) during the project’s three data collection points will be informed about and asked to participate in the study at baseline and follow-ups I and II. Although the risk for urinary retention increases with age, and most hip surgery patients are becoming of advanced age, we will not exclude younger patients and thus discriminate due to age. Rather, inclusion criteria besides being admitted for hip surgery encompass the ability to communicate in Swedish without an interpreter, whilst a diagnosed cognitive impairment is an exclusion criterion.

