**Methods:**

Twenty orthopaedic sites are cluster randomised into intervention and control sites, respectively. The intervention sites assemble local facilitator teams among nursing and rehabilitation staff, including first-line managers. The teams receive a 12-month support programme, including face-to-face events and on-demand components to map and bridge barriers to guideline implementation, addressing leadership behaviours and de-implementation of unproductive routines. All sites have access to the guidelines via a public healthcare resource, but the control sites have no implementation support.

Baseline data collection includes structured assessments of urinary retention procedures via patient records, comprising incidence and severity of voiding issues and complications, plus interviews with managers and staff, and surveys to all hip surgery patients with interviews across all sites. Further assessments of context include the Alberta Context Tool used with staff, the 4Ps tool for preference-based patient participation used with patients, and data on economic aspects of urinary bladder care.

During the implementation intervention, all events are recorded, and the facilitators keep diaries.

Post intervention, the equivalent data collections will be repeated twice, and further data will include experiences of the intervention and guideline implementation.

Data will be analysed with statistical analyses, including comparisons before and after, and between intervention and control sites. The qualitative data are subjected to content analysis, and mixed methods are applied to inform both clinical outcomes and the process evaluation, corresponding to a hybrid design addressing effectiveness, experiences, and outcomes.

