### The implementation strategy

The OPTION intervention builds on the renowned Integrated Promoting Action on Research Implementation in Health Services (i-PARiHS) framework [31, 32] and the Ottawa Model of Implementation Leadership, O-MILe [33–35]:

The OPTION study trials a multi-professional, multi-level strategy: the orthopaedic units in the intervention group select their teams as above and are expected to serve as facilitators as individuals and as a group, enabling others to adapt the guidelines and addressing attitudes and routines that can pose barriers to such adaptation, including de-implementation of outdated or redundant praxis [29]. The 10 intervention units will receive the support programme for teams, whilst the 10 control group units will receive no support. Nevertheless, both the intervention units and the control units have and have had unlimited access to guidelines as described above.

An overall plan for the events and timing is provided in Fig. 3.
E-meet and seminar. Half-day or full-day seminars for all IF teams (including first-line managers) via video link or face-to-face venues. Scaffolding the local team and overall team building, some sessions will be for both IFs and managers, and some separate, addressing more specifically the IFs in terms of the clinical issues re urinary retention and knowledge translation [36, 37] and the managers in implementation leadership [26–28]. The purpose is for the IFs and managers to learn and share, including progress and experiences.Web. Providing the teams with tools and sources via the unique web page which they can access 24/7, with opportunities to post queries, this will provide on-demand support during the intervention and also build a resource bank, including FAQs, on guideline implementation and de-implementation of low-value care related to urinary retention matters.Open space. Opportunities to meet with the researchers (i.e. external facilitators) to consider and settle local issues and processes for implementation of evidence-based urinary retention care.

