### Data collection

The primary outcome measure for OPTION is:
Adherence to urinary retention guidelines in the care of patients undergoing hip surgery.

Additional outcomes are:
A.Incidence of and severity of urinary retention, bladder distension, and voiding complications among hip surgery patients (WP1, WP4 and WP5).B.Activities and experiences of urinary retention, bladder distension, and voiding complications care among nursing and rehabilitation staff in orthopaedic care (WP1, WP3, and WP5).C.The IFs’ and managers’ experiences of the facilitation programme (WP2 and WP5).D.The patients’ experience of bladder care and voiding self-care management during the hospital stay and post discharge, including conditions for participating in these health-related issues (WP1, WP4, and WP5).E.Use and costs of urinary retention devices and labour related to bladder monitoring (WP5).

Hence, data will be collected as follows:

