A.Quantitative data regarding urinary retention will be collected from patient records, including bladder monitoring, voiding and healthcare interventions, by means of a structured template [12, 22] at baseline, post completion of the study intervention, and an additional, 1-year follow-up.B.Structured patient record assessment in triangulation with qualitative interviews with a random sample of nursing and rehabilitation staff and managers across all sites [13, 23, 25, 38]. In addition, baseline data collection includes mapping the context, with the Alberta Context Tool (ACT) [39, 40] distributed among all nursing and rehabilitation staff.C.Qualitative interviews post intervention (follow-ups I and II), in addition to voice recordings of all events during the intervention (support programme) [13, 23, 41]. Further, IF teams and managers will be asked to keep notes, by means of an individual, semi-structured reflective diary [42].D.Structured patient record assessment in triangulation with a post-discharge structured survey to all hip surgery patients for voiding difficulties after the hospital episode, self-care management and conditions for participating in accordance with one’s preferences—the latter using the 4Ps tool (Patient Preferences for Patient Participation) [43–45]. Further, data will originate from qualitative interviews with a sample of two patients per data collection point and site, representing the age range and gender distribution among those having had hip surgery.E.The structured patient record assessments at baseline, follow-up I and follow-up II will inform the health economics evaluation.

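### At follow-ups I and II patients are asked one by one to take part at sites that know their arm, and the named tests are unadjusted, so differential enrolment could bias the comparison uncorrected

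*Protocol article*

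**What the plan says.** All places are in the protocol article.

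- **Randomisation** (Power and sample): "Once the units had agreed and the ethics board had approved the trial, the randomisation was performed". It is not tied to completion of any patient enrolment.
- **Open allocation** (The implementation strategy): "The 10 intervention units will receive the support programme for teams, whilst the 10 control group units will receive no support". The programme lasts 12 months and involves first-line managers as well as staff.
- **Patient entry** (Participants, Patients): hip surgery patients in any unit "during the project’s three data collection points will be informed about and asked to participate in the study at baseline and follow-ups I and II". Eligibility also requires being able to communicate in Swedish without an interpreter and having no diagnosed cognitive impairment. These criteria are the same in both arms.
- **Primary outcome** (Data collection): "Adherence to urinary retention guidelines in the care of patients undergoing hip surgery".
- **Data source** (Data collection, item A): "Quantitative data regarding urinary retention will be collected from patient records, including bladder monitoring, voiding and healthcare interventions", using a structured template at three time points.
- **Comparison** (Abstract, Methods): statistical analyses "including comparisons before and after, and between intervention and control sites".
- **Between-group tests** (Data analysis): Student's t test, the Mann–Whitney U test and "a χ2 test for nominal variables". No covariate is named.

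**The concern.** Randomising sites balances sites in expectation. It does not balance which patients are later asked and agree. When individuals are recruited after allocation is known, the share approached or agreeing can differ by arm, and so can the type of patient enrolled. A difference in adherence or in retention that comes from enrolment would then be read as an effect of the implementation programme. A larger sample does not reduce this bias, and neither does a correction for clustering.

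The article itself treats case mix as a source of bias. Power and sample says that university hospitals were split equally between arms to guard against differences in the complexity of patients' medical status. That protection works at site level only. Setting and inclusion criteria treats elective-only units as equal to units that also do fracture surgery. Fracture/elective status is not one of the four randomisation steps. Nothing stated keeps the enrolled fracture share alike in the two arms.

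**Working it through.** **Step 1: order of events.** Sites are randomised, the programme runs openly for 12 months in one arm, and new patients are then informed and asked at follow-ups I and II. For those two waves, recruitment after known allocation follows from the text. For baseline it does not, because the timing figure (Fig. 2) is not shown.

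**Step 2: does agreement govern the primary outcome?** The Patients section describes only patients who are asked to participate. Data collection draws bladder-care data from patient records. Read together, they imply that records are reviewed for those who agree. No sentence says so, and none contradicts it.

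**Step 3: the plan's own sample size.** Inputs from Power and sample: 50% versus 65% adherence, 90% power, two-sided 0.05, intracluster correlation 0.03, 10 clusters per arm.
- The pooled-variance formula for two proportions gives 227 per arm, as stated.
- Cluster size: m = n(1 − ρ)/(k − nρ) = 227 × 0.97/(10 − 6.81) = 69.0. Then 20 × 69 = 1380, as stated.
- Design effect: 1 + 68 × 0.03 = 3.04. Effective size per arm: 690/3.04 = 227.
- Standard error of the difference at 50% adherence: √(2 × 0.25/227) = 0.047.

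These figures only set the scale for the next two steps. They do not bear on whether the concern holds.

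**Step 4: illustration by case mix.** Both inputs are assumed; neither is in the article.

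Bias = (difference between arms in enrolled fracture share) × (difference in adherence between fracture and elective patients).

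| Share difference | Adherence gap | Bias |
|---|---|---|
| 0.05 | 0.10 | 0.5 points |
| 0.10 | 0.20 | 2 points |
| 0.20 | 0.30 | 6 points |

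With the standard error above, a bias of 2 points raises the two-sided type I error from 5% to about 7%. A bias of 6 points raises it to about 25%.

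**Step 5: illustration by care received.** All inputs are assumed. True adherence is 50% in both arms and the control arm is unselected. In the intervention arm, enrolment is c₁ for patients cared for according to the guideline and c₀ for the others. Observed adherence = 0.5c₁/(0.5c₁ + 0.5c₀).

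| c₁ | c₀ | Observed | Spurious difference | Type I error |
|---|---|---|---|---|
| 0.70 | 0.65 | 51.9% | 1.9 points | about 7% |
| 0.70 | 0.60 | 53.8% | 3.8 points | about 13% |
| 0.70 | 0.50 | 58.3% | 8.3 points | about 43% |

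These error rates already allow for clustering through the design effect. Steps 4 and 5 are two separate mechanisms, so neither confirms the size of the other.

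**The case against.** **The central premise is inferred.** The article never says that record review is limited to patients who agree. Joining the study also covers a survey and interviews, and item A of Data collection does not mention consent. This stands, so the point is conditional.

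**The details may be elsewhere.** Who invites, when, and under what consent or waiver is commonly left to the full protocol. This stands too, and the article's silence on these matters is not part of the point. The point rests on what the article does fix: individual invitation at waves after open allocation, and unadjusted tests.

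**Everyone may already be invited.** The Patients section covers hip surgery patients in any unit during the collection points, and the survey is meant for all hip surgery patients. That reads as inviting all comers, which weakens any suggestion of picking patients. Differential agreement remains possible.

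**A stronger reading.** A reader might infer that ward staff in intervention sites approach patients at the bedside and favour those whose bladder care went well. The article does not support this. It names neither the recruiter nor the setting, and it says nothing of staff motives.

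**Before-and-after comparison.** Selection that is constant over time within a site would largely cancel in a comparison of changes. Selection that shifts once the programme has run would not.

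**Site mix.** Some units do elective surgery only, so fracture share can also differ by arm because of which sites fell where. That is a separate matter, although the same adjustment would help with it.

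**Conclusion.** The point holds in conditional form. At follow-ups I and II patients are asked individually at sites that know their arm. If adherence is then measured only in those who agree, case mix can differ by arm, and none of the named tests would correct for it. Bias is possible, not shown.

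Its size cannot be derived from the article. The range of 0.5 to 6 points, with a middle case of 2 against the planned 15, depends wholly on assumed inputs. So do the 1.9 to 8.3 points under selection on care received.

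Two further inferences are not supported. One is that baseline patients were also recruited after allocation was known, since that order is not shown. The other is that the enrolled groups will in fact differ.

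**What to change.** 1. At each wave, take consecutive eligible patients from the operating list from a fixed start date until the site's target is reached (1500/20 = 75 on average). Use the same invitation procedure in both arms.
2. If the ethics approval allows, extract record-based adherence for every patient on that list, whether or not the patient joins the survey or interviews. This removes the dependence on agreement. If it is already the plan, say so; the main part of this point then falls away.
3. Report the numbers operated, eligible, invited and agreeing by site and arm.
4. Replace the unadjusted primary comparison with one adjusted for age, sex and fracture/elective status that also accounts for site.

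The cost is a list count per site and slightly more analysis work. Item 4 covers measured case mix only and would not remove selection on the care received, so items 1 and 2 matter more. There is no need to require that consent be sought only after discharge by the research team. That would keep the agreement step and might lose frail patients.
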